## Abstract

**Background:**

Chronic
pain is a prevalent and costly problem that often has occupational origins. Home care workers (HCWs) are at high risk for work-related injuries, pain, and disability. Current treatments for chronic pain emphasize medications, which are an inadequate stand-alone treatment and can produce significant adverse effects.

**Methods:**

In this translational study, we will adapt an established work-based injury prevention and health promotion program (COMmunity of Practice And Safety Support: COMPASS) to address the needs of HCWs experiencing chronic pain. COMPASS employs peer-led, scripted group meetings that include educational content, activities, goal setting, and structured social support. The translated intervention, named COMPASS for Navigating Pain (COMPASS-NP), will be delivered in an online group format. Safety protections will be strengthened through an ergonomic self-assessment and vouchers for purchasing ergonomic tools. Educational content will integrate a self-management approach to chronic pain using proven cognitive-behavioral therapy (CBT) principles. We will use a mixed-methods hybrid type 2 evaluation approach to assess effectiveness and implementation. A cluster-randomized waitlist control design will involve 14 groups of 10 HCWs (*n* = 140) recruited from Washington, Oregon, and Idaho. Half of the groups will be randomly selected to complete the intervention during the first 10 weeks, while the waitlist groups serve as controls. During weeks 10–20, the waitlist groups will complete the intervention while the original intervention groups complete a follow-up period without further intervention. Our primary hypothesis is that COMPASS-NP will reduce pain interference with work and life. Secondary outcomes include injury and pain prevention behaviors, pain severity, changes in medication use, risk for opioid misuse, well-being, physical activity, and sleep. Qualitative data, including phone interviews with group facilitators and organizational partners, will evaluate the implementation and guide dissemination.

**Discussion:**

The results will advance the use and knowledge of secondary prevention interventions such as ergonomic tools and cognitive behavior therapy, to reduce injury, pain, and disability and to encourage appropriate uses of analgesic medications among HCWs.

**Trial registration:**

ClinicalTrials.gov NCT05492903. Registered on 08 August 2022

**Supplementary Information:**

The online version contains supplementary material available at 10.1186/s13063-023-07149-8.

## Background

Chronic pain is a prevalent problem impacting many people’s lives. According to the International Classification of Diseases of the World Health Organization, chronic pain is defined as persistent or recurrent pain lasting longer than 3 months [1]. Chronic pain, defined as pain that is experienced every day for the preceding 3 months or more, affects 11.2% of US adults, and 41% of those with daily pain report the pain is severe [2]. In addition to the suffering and losses experienced by those affected, there are impacts on family and friends, as well as societal costs in compensation payments and lost productivity [3]. Common treatments for chronic pain emphasize analgesic medications, regional anesthesia, and surgeries. These treatments have significant risks and side effects, and their effectiveness as stand-alone tactics is limited [4, 5]. However, when coupled with pain self-management education and cognitive-behavioral therapy (CBT), treatment effectiveness increases [6]. Although such tertiary prevention approaches can provide substantial benefits, they can be costly and require a substantial time commitment from patients (e.g., full-day programs extended for up to 6 weeks), and there is limited availability. There are important opportunities for earlier interventions. For people who work full time, the workplace represents at least 50% of their exposures to physical injury and pain-inducing hazards [7]. The current project focuses on a work-based secondary prevention approach to address and interrupt the progression of pain and associated problems within an at-risk working population.

Home care workers (HCWs) are a growing and vulnerable working population that bears a great burden of pain and associated problems. There are an estimated 3.6 million home care workers (HCWs) and personal care aides in the USA, and the occupation is expected to grow 25% by 2030 [7]. HCWs are predominantly low-income, older (mean age mid-40 s), female, increasingly immigrants, people of color, and ethnic minorities [8]. Common home care tasks pose musculoskeletal injury hazards when performed alone or without ergonomic equipment or tools and include bathing, transferring, and transporting clients and performing housekeeping tasks (e.g., making beds, scrubbing walls/floors) [9]. In 2020, the lost time injury rate for home health and personal care aides was 166.9 per 10,000 full-time workers, compared to 120.7 for all occupations. Lumbosacral pain is prevalent among HCWs, and those exposed to client moving/transferring tasks also experience chronic pain in their upper extremities [9]. HCWs reported in 2020 a rate of general soreness and pain that was nearly double that of all occupations combined (27.0 vs. 15.4 per 10,000 full-time workers) [10]. As a financial necessity, the majority of HCWs with injuries or pain continue to work [11], placing them at risk for exacerbations of pain, re-injury, worsening chronic pain, related disability, and opioid misuse.

Surveillance research with HCWs in Washington state investigated the prevalence of pain, workers’ pain management strategies, and opioid misuse risk. In that study, 54.2% of respondents met the study-specific criteria for elevated pain (i.e., self-reported experiences of pain worse than normal in the last week or perceived need for daily pain medication) [12]. Over-the-counter medications were the predominant pain management strategy reported by 67.3% of HCWs in the sample, with 4.8% reporting current prescription opioid use. Elevated pain, as well as several biopsychosocial factors (e.g., injuries, financial strain, depressive symptoms), was significantly associated with opioid misuse risk [12]. Opioid use, and potential misuse, in this middle-aged population is a priority topic. Between 1999 and 2015, this demographic experienced a staggering 471% increase in prescription opioid-related overdoses.

There is a clear need for practical resources and interventions for HCWs experiencing chronic pain that address their uniquely demanding work exposures and barriers. HCWs are an isolated and dispersed workforce and have access to fewer occupational safety and health protections and supports than more typical workers, such as safety committees, hazards assessments, ergonomic tools, physical assistance from co-workers, and supervision. Moreover, HCWs’ workplaces are their clients’ private residences. Clients are rarely aware of safety standards or the importance of ergonomic equipment (e.g., mechanical lifts) and tools (e.g., slide boards) for protecting workers [13]. Qualitative research indicates that HCWs face many barriers to acquiring ergonomics tools, forcing them to purchase their own tools, improvise with potentially dangerous homemade tools, or do without [14]. Assessing task demands, tool needs, and reducing barriers to accessing ergonomic assistive devices are important work-based areas for primary and secondary injury and pain prevention interventions [12].

When primary prevention fails and injury occurs, work-based injury rehabilitation and return-to-work programs are important for reducing disability and improving functioning [15]. However, dominant approaches to rehabilitation provide support only after problems have become severe and emphasize physical functioning and outcomes like absence and productivity [16–20]. Both return-to-work programs and medication-only treatments tend to neglect important causal drivers of impaired functioning such as pain severity, emotional distress, and pain interference with multiple work and life domains and also underemphasize the role of workers’ cognitive and behavioral strategies for managing their symptoms.

Alternative and complementary approaches promoting the management of chronic pain through non-pharmacological strategies have been established as a public health priority by the United States Department of Health and Human Services and the National Academies of Sciences, Engineering, and Medicine [21, 22]. The Centers for Disease Control and Prevention and Department of Health and Human Services [21] have called to broaden the scope of chronic pain treatment and coverage to include methods, such as cognitive-behavioral therapy (CBT) for pain management, in part to reduce pain progression, disability, and prescription opioid use and misuse [23]. The workplace presents an important and potentially powerful locus for interventions of this type; however, the few work-based pain management interventions to integrate CBT have lacked strong safety and ergonomic protections that are fundamental for injury and pain prevention [24–26]. None has extended CBT to HCWs with chronic pain.

### Rationale

To address the problems of work-related injury, pain onset and exacerbation, and potential medication misuse among HCWs, the current project will translate an established intervention for injury prevention developed for HCWs to address the special needs of those who are experiencing chronic pain. The original COMmunity of Practice And Safety Support (COMPASS) intervention, created and evaluated within the Oregon Healthy Workforce Center (OHWC), is a group program that employs peer-led, scripted meetings. A professional trainer or facilitator conducts the initial meeting to demonstrate the process, and then workers take turns serving as peer leaders. Meetings include educational content (i.e., diet, exercise, use of low-tech ergonomic tools, and client communication), activities, goal setting, and structured social support [27–29]. Clusters of HCWs (16 clusters, *n*= 149 workers) were randomized to intervention and control conditions. The intervention involved 12 monthly peer-led and scripted meetings. Evaluation data were collected at baseline, 6 months (mid-intervention), and 12 months (post-intervention). Relative to control, the intervention produced improvements to injury protective safety practices and included the use of ergonomic tools or techniques for physical work, safety communication with clients, and hazard correction in homes. Injury-related lost work days also significantly reduced [28].

The COMPASS study did not directly address chronic pain management, and consequently, reductions in pain severity were small and non-significant [27]. Our qualitative analysis revealed there were persistent barriers for HCWs to access ergonomic tools that are typically not covered by insurance (e.g., slide boards, long-handled cleaning tools). We also found that obtaining tools is exhausting and stressful for low-wage HCWs, who are often forced to buy their own, improvise with untested homemade tools, or do without [14]. To explore the potential differential effects for HCWs with pain in the original COMPASS trial, secondary analyses were conducted with intervention group participants focused on safety and mental health outcomes. In a generalized linear mixed model, HCWs with pain limitations [30] at baseline showed a trend (*F*[1,60] = 2.11, *p* = 0.15) of making larger 6-month increases in the mean safety actions (Cohen’s *d* = 0.75) compared to those without limitations (Cohen’s *d* = 0.44; difference-in-difference Cohen’s *d* = 0.31). However, workers with pain limitations experienced a trend (*F*[1,57] = 0.73, *p* = 0.40) of worsening mental health [31] (Cohen’s *d* =  − 0.08) compared to improvements (Cohen’s *d* = 0.11) experienced by those without (difference-in-difference Cohen’s *d*= 0.19). One interpretation is that workers with pain tried harder to achieve pain relief, but without pain education and CBT pain management strategies, they experienced less intervention benefit for mental health. The lack of pain-specific content, barriers to accessing tools, and differential outcomes for HCWs with pain highlight the need for a translated version of COMPASS. Therefore, COMPASS for Navigating Pain or COMPASS-NP will be implemented with virtual web-based groups to maximize availability, efficiency, retention, and dissemination potential. The intervention translation plan includes strengthening ergonomic protections, adapting established educational content for workers experiencing chronic pain, and integrating new content focused on pain self-management and CBT strategies [6, 32, 33].

Theoretical and conceptual foundations of the base [34] and planned translated intervention include community of practice theory [35], the social cognitive theory of self-regulation [36], reinforcement or operant learning theory [37], and *Total Worker Health*® approaches to workplace interventions [38]. COMPASS-NP will expand these foundations to include CBT strategies for pain self-management. The cognitive-behavioral perspective and techniques outlined in CBT for pain management [39] are aligned with the biopsychosocial model of pain [40]. CBT for pain management is specifically designed to build perceived control and self-efficacy for managing pain [41]. Components of CBT have been effective in prior workplace interventions [25, 42, 43], with lower educated individuals [44, 45]. Research supports the efficacy of CBT for improving physical and emotional functioning and reducing pain-related disability [42, 46]. CBT is often combined with other strategies to bolster effectiveness. For example, when combined with exercise [47, 48] and sleep hygiene interventions, CBT produced significantly better pain outcomes relative to control or single-strategy conditions. These perspectives and strategies focus on altering individuals’ appraisal of their pain, interpretation of causes and responses, and advancing skills and self-efficacy for managing pain. These emphases are designed to influence individuals’ expectations, acceptance of treatment and their role in pain self-management, adherence to and responses to treatment (e.g., improved physical and emotional functioning, reduced pain interference with life, reduced dependence on pharmacologics) [49]. Specific skills are taught in CBT that center on pain self-management strategies, such as goal setting, problem solving, self-monitoring of pain and coping, physical activity pacing, and prevention through protective and healthy lifestyle practices.

The current study is a translational research project within the OHWC – a NIOSH Center of Excellence for *Total Worker Health*(TWH). The Center’s current theme is “intervention effectiveness, translation, and outreach to advance safe and healthy work design.” TWH is defined by NIOSH as “policies, programs, and practices that integrate protection from work-related safety and health hazards with promotion of injury and illness-prevention efforts to advance worker well-being” [38].

Our primary outcome, pain interference, is a widely used target in pain intervention research. It is inclusive of pain-related physical limitations but also addresses pain interference with additional work-life domains (e.g., relationships, sleep, enjoyment of life). Thus, our primary hypothesis is that COMPASS-NP will have more reduction in pain interference with work and life in the intervention group relative to the control group. Our secondary outcomes will evaluate injury and pain prevention behaviors (e.g., ergonomic tool use), occurrence of injuries, pain severity, changes in medication use, risk for opioid misuse, worker well-being, and objective measures of physical activity and sleep (i.e., actigraphic). Implementation measures will explore the process differences across partners’ systems and assess the intervention fidelity and acceptability. Our secondary hypotheses assert that these outcomes will change in favorable directions relative to the control group. These measures will include environmental and system characteristics, HCW attendance and participation in group meetings, HCW and facilitator characteristics and qualitative feedback, and HCW ratings of the acceptability of the goals, processes, and outcomes of the intervention.

## Methods/design

The goals of our translational intervention research are to provide HCWs with an effective work-based program to prevent injuries/re-injury, build pain self-management skills, and reduce pain interference with work and life. To maximize intervention reach and dissemination potential, COMPASS-NP will be implemented and evaluated in an efficient Internet-based format. Original COMPASS materials will be enhanced with the addition of an online ergonomic self-assessment and a voucher for purchasing tools. We will also adapt existing educational modules to address the needs and limitations of HCWs with elevated pain and create new specific educational modules focused on CBT strategies for pain self-management based on *The Pain Survival Guide *[50]*.* Our specific aims are to (1) pilot COMPASS-NP in Oregon, (2) determine the effects of COMPASS-NP across three states (i.e., Oregon, Washington, and Idaho), (3) describe the translation and implementation of COMPASS-NP across partners and systems, and (4) disseminate COMPASS-NP knowledge, tools, and toolkits.

This protocol has been written according to the recommendations of the SPIRIT 2013 statement [51]. SPIRIT provides guidelines that define the standard elements of a protocol, including recommendations for intervention trials. A completed checklist can be found in Additional file 1: SPIRIT Guidelines.

### Participants, recruitment, randomization, and statistical power analysis

HCWs (*n* = 140) with the presence of symptoms of chronic pain will be recruited across Oregon, Washington, and Idaho to participate in this study with the help of our partner organizations: the Oregon Home Care Commission, the Service Employees International Union (SEIU) 775 Benefits Group in Washington, and the St. Luke’s Health System in Idaho. We will perform 1:1 randomization of block size 2 within each state. The randomized groups will be computer generated by the study statistician and kept in sealed envelopes.

The effectiveness and implementation of COMPASS-NP will be evaluated using a mixed-methods hybrid type II evaluation approach [52]. In this cluster randomized waitlist control design, all HCWs will participate in the trial for 20 weeks, with measures collected by online surveys at baseline, 10 weeks (follow-up 1), and 20 weeks (follow-up 2) (Fig. 1). Fourteen groups of 10 workers each will be created based on residence in the same state and schedule availability for attending group meetings. Half of the recruited groups in each state will be randomly selected to complete the intervention during the first 10 weeks, while the remaining groups serve as wait-list controls (i.e., delayed start) during the same period. After 10 weeks, the wait-list groups will initiate the intervention and finish at week 20. Original intervention participants will experience usual practice during weeks 10 to 20. A randomized waitlist study design was chosen because it creates an intervention vs. control group comparison but also permits every participant to eventually receive the intervention. Given our focus on a vulnerable population in high need of interventions, we deemed this to be the best and most ethical approach for our project.

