**Fig. 1 Fig1:**
[figure not shown]
Participant timeline

The sample size target of 140 (70 in the intervention group, 70 in the waitlist control group) was based on an a priori power analysis to achieve 80% power to detect a moderate effect size (*d*= 0.50) between the groups at 10 weeks on our primary outcomes. Our sample size requirement assumes a conservative 20% attrition at each time point (original COMPASS study saw 15% attrition at 12 months) [27]. We also assumed an AR(1) correlation structure with rho = 0.7 for repeated observations within each worker. The power calculation also takes into account a conservative intracluster correlation coefficient within each virtual group of 0.10 (in the original COMPASS trial, ICC range was 0.001–0.086) [27]. The estimated effect size of *d* = 0.50 is the average effect size for safety changes at 6 months in the original COMPASS trial, which represents a reasonable estimated effect for COMPASS-NP for pain-related limitations outcomes.

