### Inclusion/exclusion criteria

The inclusion criteria will consist of adult HCWs reporting chronic pain (pain lasting 3 + months and > 4 average intensity), the current presence of pain interference with work (response of “agree” or “strongly agree” on single-item), currently working ≥ 4 h per week, and access to the Internet with a video-capable device (e.g., smartphone, tablet, or computer). The exclusion criteria will include prior exposure to the original COMPASS program, childbirth in the prior 6 months or current pregnancy, major surgery in the prior 6 months or scheduled major surgery during the study period, and any significant psychiatric problems resulting in hospitalization during the prior 6 months.

Study partner organizations will send HCW recruitment emails and also advertise the opportunity through websites, newsletters, and other established communication channels (e.g., social media). Interested HCWs will complete an online eligibility screener survey along with their schedule availability and technology comfort level. Qualifying HCWs will be contacted by the study staff by phone to discuss the study and complete an informed consent process. Once 2 groups of 10 HCWs in the same state are created, those groups will be randomized. The group receiving the intervention first will be mailed program materials and then contacted by their facilitator to schedule a pre-program call for coaching on web-based technology for group meetings.

COMPASS-NP group facilitators will be recruited from existing professional trainers or staff from partner organizations and complete training prior to leading groups (see the “ Intervention condition” section).

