### Data analysis, storage and fidelity

#### Quantitative data analysis

We will summarize participant demographics using descriptive statistics and data visualizations (e.g., histograms, scatter plots) to evaluate the differences between study arms. Effectiveness analyses will employ an intent-to-treat approach where participants are analyzed and included according to their randomized condition [77], regardless of their degree of intervention participation. This approach also utilizes all available data from participants across all time points. To test our hypothesis that the intervention group will experience reduced pain interference with work and life, we will evaluate the within- and between-group differences in the magnitude of change in the two primary outcome domains, using a difference-in-differences (DID) approach that suits the between-group and within-group design of this study. The DID approach is a general approach that can estimate relative changes in outcomes within-group and between study groups through a group-by-time interaction group. Specifically, we will implement our DID approach using generalized linear mixed models (GLMM) [78], which offer flexible regression modeling to accommodate for different sources of correlations (e.g. serial and intra-group), categorical and continuous covariates, and fixed and time-dependent covariates. These GLMMs offer a wide range of parametric distributions to model the dependent variables, including logistic regression (binary data), beta regression (percent data), Poisson regression (count data), and Gaussian regression (normally distributed data). For example, to assess the changes in pain interference, a Gaussian linear mixed model can analyze pain interference at baseline, week 10, and week 20 as a function of whether a HCW belongs to the intervention condition, time, the interaction of condition and time, and other potential confounders (e.g., psychosocial factors from our background survey). We will operationalize comparisons by computing interaction contrasts on pre/post-intervention differences within and across groups. Intervention group membership will be the between-subjects factor and pre/post-intervention assessment scores on primary outcomes will be the within-subjects factors. The interaction contrast approach will allow us to efficiently compare the 2 study arms at the end of 10 and 20 weeks on each pain interference measure with a focused, one degree of freedom hypothesis test. Additionally, to take advantage of the full longitudinal data set (baseline, 10- and 20-week time points), we will implement an analysis of response profiles to characterize the patterns of change in the mean response over time in the two arms by treating time as a categorical factor. Our approach will include random effects for virtual group clusters to account for the correlation of outcomes within virtual groups. We will also include random effects for HCWs to account for the correlation of observations within a worker over time. Depending on the distribution of the outcomes of interest, standard errors may be difficult to estimate using standard regression variance output. Thus, if we cannot accurately represent standard errors, we plan to implement bootstrapping to obtain reliable standard errors when appropriate. If imbalances in participant characteristics are observed at baseline, we will consider propensity score weighting to improve efficiency [79]. We will explore missing data and apply standard practices to control for the differences between subjects in missing data or to impute scores if non-trivial levels of missing data are observed. Similar analytic methods will be applied to secondary outcomes, with appropriate adjustments based on the characteristics of the data and distributions. We will follow the CONSORT 2010 guidelines when reporting study results [80].

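### Groups are randomised in same-state pairs, but the described primary model has no term for state; if change differs by state, the standard error is somewhat too large

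*Protocol article*

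**What the plan says.** The design is stratified. Under the heading on participants, recruitment, randomization and power, the protocol article says "We will perform 1:1 randomization of block size 2 within each state" and "Half of the recruited groups in each state will be randomly selected to complete the intervention during the first 10 weeks". Under Inclusion/exclusion criteria it adds "Once 2 groups of 10 HCWs in the same state are created, those groups will be randomized". Each randomised unit is therefore one of a same-state pair. The total is 14 groups of 10, with "70 in the intervention group, 70 in the waitlist control group".

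Under Quantitative data analysis, the example model for pain interference treats the outcome "as a function of whether a HCW belongs to the intervention condition, time, the interaction of condition and time, and other potential confounders". The only example given of a confounder is psychosocial factors from the background survey. Random effects are planned for virtual group and for worker, and the test is a one-degree-of-freedom interaction contrast on change. State does not appear as a model term. Elsewhere it serves only to describe the sample and to compare systems descriptively.

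**The concern.** An analysis normally reflects the strata used in the randomisation. Balance within state removes between-state variation from the sampling error of the arm difference. If the model has no term for it, that variation still sits in the estimated between-group variance. The reported standard error is then larger than the true one.

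The open covariate list does not settle this. It is worded in terms of confounders, and a factor balanced by design is not one. The propensity weighting in the same section is triggered by baseline imbalance, so it would not bring state in either. The plan thus leaves room for covariates chosen on the data, but does not name the one covariate fixed by its own randomisation.

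State differences in change are possible, since the three partners are a state commission, a union benefits group and a health system. With only 7 groups per arm, a modest excess in between-group variance could matter.

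**Working it through.** **Inputs from the protocol article:** 14 groups of 10, 7 per arm; 20% attrition, hence 8 completers per group; ICC 0.10 (0.001–0.086 in the original trial); AR(1) correlation 0.7; d = 0.50; 80% power.

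**Assumptions, not in the document:** two-sided alpha 0.05; 3/2/2 pairs per state; group effects with the same 0.7 correlation over time; all state variances.

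**1. The planned sample size.** Two means at d = 0.5 need 63 per arm. Multiply by 1 − 0.7² = 0.51 (baseline adjustment) and by the design effect 1 + 7 × 0.10 = 1.70: 63 × 0.51 × 1.70 = 54.6, rounded to 55. Then 55/0.80 = 68.75, or 69 per arm and 138 in total (136 without intermediate rounding), close to 140. State plays no part in this figure.

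**2. State differences constant over time.** These cancel from each worker's change. The per-group variance of mean change is 2(1 − 0.7) × (0.10 + 0.90/8) = 0.6 × 0.2125 = 0.1275. The standard error of the arm difference is √(2 × 0.1275/7) = 0.191, with or without state. From the noncentral t, power is 67.2% on 12 df and 65.7% on 10 df. Simulated cluster means (40,000 replicates) agree: mean standard error 0.187 without state and 0.186 with it; power about 67% and 65.5%. Here adjustment only costs power.

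**3. State explains a share s of the between-group variance in change.** The standard-error ratio is √[(V − s × ICC)/V], with V = ICC + (1 − ICC)/8.

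| ICC | V | Ratio, s = 25% | Ratio, s = 50% |
|---|---|---|---|
| 0.10 | 0.2125 | √(0.1875/0.2125) = 0.94 | √(0.1625/0.2125) = 0.87 |
| 0.04 | 0.1600 | √(0.1500/0.1600) = 0.97 | √(0.1400/0.1600) = 0.94 |
| 0.01 | 0.13375 | √(0.13125/0.13375) = 0.99 | √(0.12875/0.13375) = 0.98 |

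At s = 0 the ratio is 1. The critical t rises from 2.18 (12 df) to 2.23 (10 df), a factor of 1.023. Adjustment pays for itself once the ratio is below 1/1.023 = 0.978. That needs s above about 9% at ICC 0.10, 18% at ICC 0.04 and 59% at ICC 0.01.

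**4. Power and test level, simulated, ICC 0.10, contrast on change:**

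| State-by-time variance | Power without state | Power with state | Null rejection without state |
|---|---|---|---|
| 0.01 | 65.6% | 66.2% | 4.5% |
| 0.02 | 63.2% | 65.8% | 3.9% |
| 0.05 | 57.0% | 65.6% | 3.1% |

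Null rejection with state is about 5%. Against a group variance in change of 0.6 × 0.10 = 0.06, these variances are 14%, 25% and 45% of the between-group variance in change (for example 0.02/0.08 = 25%).

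**5. Arms compared on 10-week levels.** For state variance 0.02, 0.05 and 0.10, power is 43.4%, 40.4% and 35.4% without state, against about 45% with it.

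**6. Mixed-model fits** (40 per scenario; random intercepts for group and worker). With constant state variance 0.05, the standard error is 0.1572 without state and 0.1573 with a state main effect. With state-by-time variance 0.02 added, it is 0.1619 without state, 0.1619 with the main effect and 0.1589 with state by time. A main effect alone does nothing. These fits serve only for the relative change: their model standard errors lie below the spread of the estimates (0.18–0.21), because the simulated group effects vary over time while the model has intercepts only.

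**The case against.** The best reply is that the model text is an illustration. It is introduced as an example, says what a Gaussian model can do, and leaves the covariate list open. Nothing excludes state, and the final covariate set often belongs in an analysis plan that is not shown. That stands as a reason to treat the point as minor. It does not remove it, because the list as worded would not lead anyone to state.

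The gain may also be nil, and this stands too. The assumed shares of 25–50% have no source in the document. At ICC 0.01, the loss in critical t is at least as large as the gain. In the mixed-model fits with state-by-time variance 0.02, the half-widths are 2.18 × 0.1619 = 0.353 and 2.23 × 0.1589 = 0.354, which is no gain.

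Further, at week 10 the waitlist groups have not begun meetings, so differences between facilitators or partners can act only in the intervention arm. That is variation in the treatment effect by state, which a state-by-visit term common to both arms removes only in part. The document gives no evidence that untreated change differs by state.

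A reader might infer that the precision gained by stratifying is simply thrown away. The document does not support that: the primary contrast is on change, and constant state differences already drop out of it.

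**Conclusion.** The point holds in a limited form, at minor severity. The design stratifies by state, the described model has no term for it, and the wording on confounders would not supply one.

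If change over time differs by state, or if arms are compared on 10-week levels, the standard error is somewhat too large and the test more conservative than it would be with state. If state differences are constant over time, the planned contrast is unaffected. The possible reduction in standard error is about 0–13% over ICC 0.01–0.10 and state shares of 0–50%. At ICC 0.10 the simulated gain in power on change is 0.6, 2.6 and 8.6 points for state-by-time variances of 0.01, 0.02 and 0.05. All of this rests on assumed variances that the document does not give.

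Neither bias nor an inflated type I error follows from omitting state: balance leaves the estimate essentially unchanged, and the error is in the conservative direction. Nor is the sample size of 140 affected. The simulated power of about 67% on change arises without any state variance, so it must not be attributed to this omission.

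**What to change.** State under Quantitative data analysis that the primary model will include state and state by visit as prespecified fixed effects, because state is a stratification factor. If the week-10 comparison is instead made in a baseline-adjusted model, include state as a covariate there. A state main effect alone in the group-by-time model is not enough, since it leaves the contrast on change untouched.

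The cost is one sentence and 2 of the 12 cluster-level degrees of freedom (critical t 2.18 to 2.23), or about 1–2 points of power if there is no state-by-time variation. Terms for the seven pairs would leave only 14 − 7 − 1 = 6 degrees of freedom, so state is the cheaper way to reflect the design. The choice should be fixed before outcome data are seen, and not made to depend on whether state appears to matter.
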